**Intervention implemented**

Health care providers trained

Lay counselors trained

Integration of family planning and STI services

**Customary care provided**

Health care providers continue with current standard of care (and lay counselors, if already in place)

Patient receives prevention interventions during all routine clinic visits as follows:

From health care provider

Prevention messages

FP counseling & contraception

STI management

From lay counselor

Prevention & TX counseling

Partner HIV testing

Alcohol intervention

Patient receives current standard of care from health care provider during all routine clinic visits

**Baseline Data Collection**

Questionnaire administered

**Comparison Clinics**

**Intervention Clinics**

**Study Visit 3**

**Comparison clinics receive intervention materials and training**

Health care providers and lay counselors trained

Integration of family planning and STI services

**Study Visit 1**

**Recruitment & Screening**

Randomly selected for participation

Eligibility determined

Consent process

**HIV prevention continues as integrated standard of care in intervention clinics**

**12 Month Follow-up**

Patient completes study questionnaire

**12 Month Follow-up**

Patient completes study questionnaire

**6 Month Follow-up**

Patient completes study questionnaire

**6 Month Follow-up**

Patient completes study questionnaire

**Study Visit 2**

**Figure 2. Study flow diagram for clinic patients.**

Health Care Provider and Lay Counselor Assessment

Prior to attending the training for the interventions, health care providers and lay counselors in the intervention clinics will be asked to complete baseline questionnaires about the services they deliver in their clinic and their routine standard of care with patients (Appendix I). At 6- and 12-months following implementation of the interventions, they will be asked to complete questionnaires about the acceptability of the intervention messages, materials and protocol, as well as the feasibility of implementing these prevention interventions into HIV care and treatment settings (Appendix J). In addition, they will be asked about the fidelity with which they have been able to implement them.

Health care providers in the comparison clinics will also complete baseline questionnaires about the services they deliver in their clinic and their routine standard of care with patients. The questionnaires will be completed again at 6- and 12-months in order to determine whether there were any changes in types of services delivered. If counselors are also in place in the comparison clinics as usual standard of care then they will complete the lay counselor questionnaires.

Additionally, project staff will observe about 3% of provider clinic visits and lay counselor counseling sessions in both the intervention and comparison clinics. The project staff will approach the provider or lay counselor and request permission to observe a patient visit. The provider or lay counselor will ask the patient for permission to have their clinic visit or counseling session observed. If the patient agrees, he/she will sign a consent form (Appendix F) granting permission to be observed. No personal or identifying information will be obtained from the patient, and they may or may not be enrolled in this project, given that this is a clinic-based intervention. The project staff will complete an observation checklist during the visit documenting the HIV prevention interventions that were discussed or delivered during the visit.

Medical Chart Review and Clinic Records Review

Clinic Services: The Clinic Services Form (Appendix O) captures HIV care and services delivered as well as contraceptives and STI treatment medications dispensed to HIV-positive patients at the clinic level. This will be completed by the project coordinator monthly in all clinics. The project coordinator will gather this clinic-level information from clinic records and clinic administrators.

Medical Chart Review: After each participant’s follow-up visit the study interviewer or coordinator will use the patient’s medical chart to gather information such as the clinic visits since last extraction, clinical indicators of HIV (e.g., CD4 count, WHO classification), medications, partner’s HIV status, reproductive health history, STI treatment provided (see Appendix P).

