**Table 2. Data collection time periods for project measures.**

|  | **Baseline** | **6-Month**  **Follow-up** | **12-Month Follow-up** |
| --- | --- | --- | --- |
| **Patient Questionnaire** | X | X | X |
| **Provider Questionnaires**   - Clinic Services - Integration of HIV prevention into care and treatment | X  X | X  X | X  X |
| **Lay Counselor Questionnaire**   - Integration of HIV prevention into care and treatment | X* | X* | X* |
| **Provider and Counselor Observation Checklist** | X | X | X |
| **Medical Chart Review and Clinical Records Review** |  |  |  |
| Clinical Services Form | X | X | X |
| Patient Medical Chart Review Form | X | X | X |

* Only at intervention clinics

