***Health care provider questionnaires***

The health care provider questionnaires will be administered at baseline, 6-months, and 12-months (see Table 2).

Clinical Care Survey: Health care providers in all clinics will be asked to document the types of care they provide to patients (Appendix I). This includes the number of patients they see per day, the amount of time they spend with them, frequency of discussing a variety of topics with patients during routine visits, and whether they provide various services or refer to other clinics for those services.

Integration of HIV Prevention into Care and Treatment: Health care providers at all clinics will provide information to assess whether and how often they addressed the topics in the intervention protocol (Appendix J). This includes use of the job tools/aids, whether they thought it was feasible and important to deliver the messages, and whether patients were comfortable receiving these messages from the health care providers. Additionally, the health care providers will answer questions about the impact of providing the intervention on the patients and the health care providers, as well as perceptions of clinic staff responsibility to provide HIV prevention interventions to patients.

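### The data-collection procedure and Table 2 disagree on the provider and counselor questionnaires; read literally, the procedure repeats the Clinical Care Survey only in comparison clinics

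*Protocol*

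**What the plan says.** Two parts of the protocol set the questionnaire schedule for clinic staff.

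The Study instruments section says: "The health care provider questionnaires will be administered at baseline, 6-months, and 12-months (see Table 2"). It assigns the Clinical Care Survey (Appendix I) and the Integration form (Appendix J) to providers in all clinics. Table 2 agrees: both provider rows are marked at all three time points and carry no arm restriction. The lay counselor row is marked at the same times, but with an asterisk whose footnote reads "Only at intervention clinics". The Lay Counselor Questionnaires text likewise places that form (Appendix K) in intervention clinics.

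The Data collection section, under Health Care Provider and Lay Counselor Assessment, describes something else. Before training, providers and lay counselors in intervention clinics are to "complete baseline questionnaires about the services they deliver in their clinic and their routine standard of care with patients (Appendix I"). For follow-up it says: "At 6- and 12-months following implementation of the interventions, they will be asked to complete questionnaires about the acceptability of the intervention messages". The same sentence goes on to the feasibility of "implementing these prevention interventions into HIV care and treatment settings (Appendix J"). A separate paragraph covers the other arm: "Health care providers in the comparison clinics will also complete baseline questionnaires about the services they deliver in their clinic", and "The questionnaires will be completed again at 6- and 12-months in order to determine whether there were any changes in types of services delivered". On counselors it adds: "If counselors are also in place in the comparison clinics as usual standard of care then they will complete the lay counselor questionnaires".

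**The concern.** Appendix I is where providers report how often they discuss each prevention topic (item 3), which contraceptive and STI services they provide or refer (item 5) and what has been added to the clinic in the last 6 months (item 6). To show that the package changed what providers do, the same questions are needed after training in both arms. The procedure states that purpose, detecting change in services, only for the arm in which no change is planned. For the arm being trained, it names a different form at follow-up.

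Eighteen clinics in three countries could work from either part of the protocol. A missed 6- or 12-month wave of provider reports cannot be reliably recovered afterwards.

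The counselor instructions have the same weakness. A site reading Table 2 would not give a form to counselors already working in a comparison clinic; a site reading the procedure would. Such counselors may well exist, since the background section notes that Namibia had begun placing lay counselors in HIV clinics.

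**Working it through.** No formula or power calculation is involved. The check sets the two schedules side by side and counts forms.

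| Form and group | Table 2 and Study instruments | Data collection procedure, read literally |
| --- | --- | --- |
| Appendix I, intervention providers | baseline, 6, 12 months | baseline |
| Appendix I, comparison providers | baseline, 6, 12 months | baseline, 6, 12 months (no appendix letter given; the content matches) |
| Appendix J, intervention providers | baseline, 6, 12 months | 6, 12 months |
| Appendix J, comparison providers | baseline, 6, 12 months | not mentioned |
| Counselors, intervention clinics | Appendix K at baseline, 6, 12 months | Appendices I and J named |
| Counselors, comparison clinics | no form | counselor questionnaires where counselors exist; number of administrations not stated |

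**Count for Appendix I.** The section on estimated number of participants gives about 10 providers per clinic and about 180 in total. With 9 clinics per arm, that is 10 × 9 = 90 per arm. Assume no turnover or refusal.

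- Table 2: 90 × 3 = 270 surveys per arm, 540 in total.
- Procedure, read literally: 90 × 1 = 90 in the intervention arm, all at baseline, and 90 × 3 = 270 in the comparison arm.
- Shortfall: 270 − 90 = 180, all of them intervention-arm follow-up surveys.

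**Consequence for the contrast.** The between-arm difference in change is (intervention follow-up − intervention baseline) − (comparison follow-up − comparison baseline). Read literally, the first term does not exist at 6 or 12 months, so the contrast cannot be formed from this survey.

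**Can Appendix J stand in?** No. Its items cover feasibility, importance, patient comfort, job-aid use, workload, perceived impact and staff responsibility. The Study instruments text describes it as recording whether and how often topics were addressed, but the printed form has no topic-frequency item. That information is in Appendix I item 3.

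**What else measures services in both arms?** The Clinic Services Form (Appendix O, with a monthly section, in all clinics), the chart review (Appendix P), the observation checklists (about 3% of visits in both arms) and the patient questionnaire (family planning items P1f and P1m, and provider topics in Q4). For counseling in comparison clinics there are the observations, patient items R1 to R10, and Appendix O item 1, which counts counselors not funded by the project.

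**The case against.** The strongest reply is that the procedure never says *only*. It names what is asked at follow-up and does not exclude other forms. The explicit schedule is in Table 2 and the Study instruments text, which agree with each other, and Appendices I and J both carry tick boxes for baseline, 6 and 12 months. On that view the procedure is an incomplete summary, and staff would have to disregard the table and the printed forms to lose any data. This stands as evidence of intent, and it is why the procedure, not the provider rows of Table 2, should change. It does not remove the conflict: the procedure names a specific form for each arm and visit, and those assignments differ from the schedule.

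Three stronger readings are tempting, and the protocol does not support them.

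- A reader might infer that the service-delivery outcome is lost. It is not. The objectives define it as family planning counseling and services, the Variables section draws outcome variables from patients and charts, and the instruments listed above measure services in both arms.
- A reader might infer that under the Table 2 footnote comparison-clinic counseling goes unmeasured. It does not; observation, patient report and the staffing count still describe it. What would be missing is the counselors' own report.
- A reader might infer that the procedure gives comparison-clinic counselors three forms each. It states no number.

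The omission of Appendix J for comparison providers is likewise an inference from silence.

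**Conclusion.** The contradiction is real and should be corrected, with limited consequences. If the Data collection procedure is followed as worded, about 180 intervention-arm follow-up Clinical Care Surveys are not collected, and that survey cannot compare change in provider-reported topics and services between arms. If sites follow Table 2, nothing is lost on the provider forms. The figure rests on the protocol's approximate provider numbers, on full participation, and on taking the form named for each arm and visit as the complete assignment.

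The primary outcome, the sample size and the power are unaffected. The counselor conflict is a second, smaller inconsistency: it decides whether comparison-clinic counselors report on their own practice. The citation of Appendices I and J for lay counselors is a plain mismatch, since the Study design and Study instruments sections assign them Appendix K.

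**What to change.** Rewrite Health Care Provider and Lay Counselor Assessment to match Table 2 and the Study instruments section:

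- Providers in both arms complete Appendices I and J at baseline (before training in intervention clinics), 6 and 12 months.
- Lay counselors complete Appendix K, cited as such.
- The Table 2 footnote and the Lay Counselor Questionnaires text are extended so that counselors already in place in comparison clinics also complete Appendix K, as the procedure foresees, with the visits stated.

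Keep Appendix J item 14 (job aids) open in comparison clinics. The Study instruments text asks providers at all clinics about job aids, and the item includes handouts, posters and an open category, so blanking it would discard planned data.

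Cost, measured against the literal procedure: Appendix I adds 90 × 2 = 180 intervention forms. Appendix J adds about 90 at intervention baseline and, if comparison providers are taken not to receive it, 90 × 3 = 270 in comparison clinics. The total is 180 + 90 + 270 = 540 provider forms, all already scheduled in Table 2. The Appendix K forms for comparison-clinic counselors cannot be counted from the protocol, but the procedure already plans for them. No new staff are needed.

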**Participant inclusion criteria**

Clinic patients

- At least 18 years old
- HIV-positive patients receiving care at a project clinic and seen at the clinic at least twice prior to enrollment (half of patients will be taking ARVs)
- Sexually active within the past three months
- Planning to attend the clinic for at least 1 year
- Able to provide informed consent to participate in the project
- Able to conduct interview in one of the following languages:

Kenya: English, Kiswahili and Kikuyu

Namibia: English, Oshiwambo, Damara-nama, Otjihero, Afrikaans

Tanzania: English, Kiswahili

Health care providers and lay counselors

- At least 18 years old
- Fluent/literate in the language selected for the project training
- Planning to remain at the clinic for one year
- Willing to complete project questions and agree to be observed during patient visits
- Physicians, clinical officers, and nurses who are employees of the project clinic and providing care and treatment to patients in the HIV project clinics
- Lay counselors who are providing HIV prevention services in the project clinics

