***Provider and Counselor Observation Checklists***

Assessing the effectiveness of the intervention package on behavioral, biologic, and service delivery outcomes depends on whether, and how accurately, health care providers and lay counselors deliver the intervention. In order to determine how the intervention changes service delivery, project staff will observe providers and lay counselors in the intervention clinics during approximately 3% of routine patient visits over the one year project period. Health care providers and counselors (where available) in comparison clinics will also be observed to have a complete assessment of standard of care visits and services provided in these the comparison clinics. At the beginning of each month, days will be randomly selected for observing health care providers and lay counselors. The number of observations per week will depend on the number of patients being seen at each clinic per week. For each observation, the observers will sit in as unobtrusive a place as possible in the room with the health care provider or lay counselor and will note which intervention activities are discussed with participants by health care providers (Appendix M) and lay counselors (Appendix N). Comparisons will then be made between the care provided at intervention clinics and the standard of care being delivered in comparison clinics.

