**Limitations of study**

Potential problems may arise, given that this is a large, multi-site project in a resource-limited setting; thus, alternate plans will be developed. Because attrition may be high, approximately 30% when following HIV-positive patients across one year, baseline sample size will be large to ensure statistical power to detect subtle behavior changes. Also, clinics are extremely busy with high patient volume, and providers may find incorporating the intervention into their routine clinic visits difficult. If all providers do not administer the intervention to all patients (i.e., some patients do not receive the intervention), measuring the effectiveness of the intervention will be difficult. Thus, fidelity measures (e.g., observation, questionnaires) are included in the project to ensure providers and lay counselors conduct the intervention as designed. In addition, the questionnaire data are all self-report, which is potentially subject to socially desirable responding, recall biases, or forgetting.

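### Fidelity observations: days are random, but within a day the person being rated is asked for permission and asks the patient, with no visit-selection rule and no record of refusals, so selection could occur unseen

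*Protocol*

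**What the plan says.** The Protocol describes the observations in two places.

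- **Provider and Counselor Observation Checklists** sets the sampling of days: "At the beginning of each month, days will be randomly selected for observing health care providers and lay counselors". On volume it says: "The number of observations per week will depend on the number of patients being seen at each clinic per week". It also says that the observations will be used to compare care in intervention clinics with standard care in comparison clinics.
- **Data collection, Health Care Provider and Lay Counselor Assessment** (the text after the study flow diagram) sets what happens on the day. The extent is that "project staff will observe about 3% of provider clinic visits and lay counselor counseling sessions in both the intervention and comparison clinics". Then: "The project staff will approach the provider or lay counselor and request permission to observe a patient visit". Next: "The provider or lay counselor will ask the patient for permission to have their clinic visit or counseling session observed". Finally: "If the patient agrees, he/she will sign a consent form (Appendix F) granting permission to be observed".

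Staff have agreed to observation beforehand. Participant inclusion criteria require that they be "Willing to complete project questions and agree to be observed during patient visits". The Consent process section makes this participation voluntary, with freedom to withdraw at any time.

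Limitations of study gives the measure its purpose: "fidelity measures (e.g., observation, questionnaires) are included in the project to ensure providers and lay counselors conduct the intervention as designed".

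**The concern.** Random days are a sound start, because they stop staff from knowing far ahead when they will be watched. They do not settle which visits are seen on those days. At that stage the person being rated is asked for permission and is also the one who puts the request to the patient. A provider who is rushed, or does not expect to cover the prevention topics, could decline or not ask. A patient facing a sensitive discussion could also decline. Either would tie being observed to what was delivered.

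The protocol itself makes such a link plausible: Limitations of study says that clinics are very busy, that providers may find the package hard to fit in, and that some patients may not receive it.

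Two results are at stake: the fidelity estimate in intervention clinics, and the observed difference in services between arms. If the trial showed no effect, these would help to decide between a package that does not work and one that was not delivered. Without a count of declined visits, the sponsor could neither show that selection was absent nor adjust for it.

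**Working it through.** **Step 1. Who controls each stage.**

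| Stage | Who decides | Fixed by the protocol? |
|---|---|---|
| Day of observation | Random draw each month | Yes |
| Visit within the day | Not stated | No |
| Staff permission for a visit | The provider or counselor being rated | Yes, asked at the visit |
| Request to the patient | The same provider or counselor | Yes |
| Patient consent | The patient, who signs | Yes |
| Record of declined visits | Nobody | No |

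Appendices M and N are filled in during a visit that is being watched. Both have space for why prevention was not discussed (Appendix M items 4 and 34, Appendix N item 23), but that concerns observed visits. Neither has a field for a visit that was declined.

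**Step 2. Effect on an observed rate.** The protocol gives no true delivery rate and no refusal rate, and its figure of about 3% of visits has no visit denominator, so there is no stated result to reproduce. All inputs below are assumptions. Let *d* be the true share of visits with delivery, and *r* the chance that a delivered visit is seen divided by the chance that an undelivered visit is seen. Then

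observed delivery = *d r* / (*d r* + 1 − *d*).

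Example: *d* = 0.50, *r* = 1.5 gives 0.75 / (0.75 + 0.50) = 60.0%.

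| True *d* | *r* = 0.8 | 1 | 1.1 | 1.25 | 1.5 | 2 |
|---|---|---|---|---|---|---|
| 30% | 25.5% | 30% | 32.0% | 34.9% | 39.1% | 46.2% |
| 50% | 44.4% | 50% | 52.4% | 55.6% | 60.0% | 66.7% |
| 70% | 65.1% | 70% | 72.0% | 74.5% | 77.8% | 82.4% |
| 90% | 87.8% | 90% | 90.8% | 91.8% | 93.1% | 94.7% |

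The bias is upward for *r* above 1, absent at 1 and downward below 1.

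**Step 3. Effect on the between-arm difference.** Assume true delivery of 70% in intervention and 30% in comparison clinics, a difference of 40 points.

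- *r* = 1.5 in both arms: 77.8 − 39.1 = 38.7 points.
- *r* = 1.5 in intervention clinics only: 77.8 − 30.0 = 47.8 points.
- *r* = 1.5 in comparison clinics only: 70.0 − 39.1 = 30.9 points.
- *r* = 0.8 in intervention clinics only: 65.1 − 30.0 = 35.1 points.

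The difference can move either way. It moves little here when selection is the same in both arms.

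**Step 4. What a refusal log would add.** Assume true delivery of 50%, with observation allowed in 95% of delivered visits.

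- Allowed in 80% of undelivered visits: share seen = 0.475 + 0.400 = 0.875; observed delivery = 0.475 / 0.875 = 54.3%.
- Allowed in 60% of undelivered visits: share seen = 0.475 + 0.300 = 0.775; observed delivery = 0.475 / 0.775 = 61.3%.

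If the share seen is known, true delivery among the selected visits must lie between 0.475 (no unseen visit had delivery) and 0.475 plus the unseen share. That is 47.5% to 60.0% in the first case and 47.5% to 70.0% in the second. As written, the protocol collects nothing from which these limits could be formed.

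**The case against.** The strongest reply is that the protocol already limits the problem. Days are random, enrolled staff have agreed to be observed, project staff make the approach, and nothing says that the provider picks the visit. The procedure is the same in both arms, and results are not shared with supervisors or co-workers, which weakens any motive to hide. All of this stands. It narrows the room for selection to refusals and to the unstated choice of visits within preselected days, but does not close it.

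A reader might infer that delivery will be overstated, and mainly in intervention clinics, because only staff there are checked against a package they were trained to give. The documents do not support that. They give no refusal rate, the patient can refuse too, and more frequent refusal of visits on sensitive topics would push the estimate down.

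A reader might also take observation to be the only evidence on delivery beyond self-report and charts. It is not. Patients tell interviewers who are not clinic staff which topics providers and counselors raised (Appendix H, Q4 and R6), and project staff take contraceptive, STI treatment and HIV testing counts from clinic records and log books (Appendix O). These are a partial cross-check. Q4 and R6 ask enrolled patients whether a topic came up at all in six months rather than at a given visit, and the clinic counts do not cover counseling content.

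Finally, one might call the per-visit provider permission superfluous. Staff participation is voluntary and may be withdrawn, so asking is consistent with the consent terms. The weakness is that refusals go uncounted and that the rated person asks the patient.

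The consent forms and the Field Operations Procedures Manual are not shown. If either contains a visit-selection rule or a refusal log, the protocol should cite it.

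**Conclusion.** The point holds as a weakness in a stated procedure: observed visits may be selected in a way related to delivery, and the protocol as written offers no means of detecting it. Size, direction and any arm difference are unknown. The figures above, from 44.4% to 66.7% for a true 50%, rest wholly on assumed values of *r* and only illustrate sensitivity. If refusal is unrelated to delivery, there is no bias.

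The consequence is confined to the fidelity results and the observed comparison of services. The primary outcome, self-reported unprotected sex, and its intent-to-treat analysis do not use the observations. The change is worth making because it is cheap and because these data are meant to help explain the trial's result.

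**What to change.** In Health Care Provider and Lay Counselor Assessment, and by cross-reference in Provider and Counselor Observation Checklists:

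1. On each randomly drawn day, preselect visits by a fixed rule, for example every *k*-th patient for that provider or counselor, with *k* set from clinic volume to give about 3%.
2. Have project staff obtain the patient's consent. The provider or counselor may introduce them.
3. Keep the right of both provider and patient to refuse.
4. Log every selected visit that was not observed, with who declined, clinic and arm. One added line with Appendices M and N, or a short separate sheet, is enough.
5. Report the share of selected visits observed, by arm, beside the fidelity results, and compare the observations with patient-reported services (Appendix H, Q4 and R6), noting the different time frames.

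The cost is revised wording and a brief log, with no additional observations. The downside is that project staff would approach some clinic patients who are not enrolled in the study; an introduction by the provider softens this.
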